## Methods/design

### Study aim

Our primary aim is to assess the effectiveness of an innovative package of orienting doctors and community health workers (CHW) about community perceptions on CAP barriers to qualified health care seeking plus infrastructural strengthening by (i) providing “Pneumonia Drug Kit” (PDK) (ii) establishing “Pneumonia Management Corner” (PMC) at additional primary health center (APHC) and (iii) “Pneumonia Management Unit” (PMU) at Community health center (CHC) *ALONG* with one of the 4 different behavior change communication (BCC) interventions:Intervention 1: Organizing Childhood Pneumonia Awareness Sessions (PAS) for caregivers of children < 5 years of age during a routine immunization day, using self-developed and validated Information, Education and Communication (IEC) materials, in PHCs and CHC monthly, conducted by a trained Auxillary Nurse Midwife (ANM) and project facilitators.Intervention 2: Organizing PAS on Village Health and Nutrition Day (V.H.N.D.) once a month by the Accredited Social Health Activist (ASHA) trained to conduct such sessionsIntervention 3: Combination of Both Intervention 1& 2Intervention 4: Usual Care

Outcome measure will be number of CAP treated by ANMs/doctors with medicines from PDK or treated at either PMC or PMU in interventions given by ANMs/ASHA workers.

Our second objective is to ascertain change, if any, in the types of health care providers’ service utilization for Acute Respiratory Illness (ARI)/CAP in last 12 months in children less than 5 years pre and post intervention.

Outcome measure will be number of ARI/CAP Treated by ANMs/doctors by various health care providers in the past 12 months in interventions given by ANMs/ASHA workers.

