**Table 1 Tab1:** Health Infrastructure of Lucknow Distric**t**

Health Infrastructure of Lucknow District	Number
Blocks	08
Community Health Centre (CHC)	09^a^
Total Sub Centre (SC)	345
Functional SC	331
Non Functional SC	14
Additional Primary Health Centre (APHC)	28
Accredited Social Health Activist (ASHA)	1246
Auxillary Nurse Midwife (ANM)	331
Super specialty hospitals	03
District combined hospitals	04
District hospitals	03
District Women hospitals	02
Number of AYUSH hospital/dispensary	78
Number of Ayurvedic hospital/dispensary	49
Number of homeopath hospital/dispensary	29

^a^BKT Block has two CHCs. Other 7 blocks have one CHC each

In the study, target population will be caregivers within the family of children < 5 years who were residing in the study area. No caregiver with a child < 5 years will be excluded.

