### Study design

A Community Based Open Labeled Behavioral Trial conducted in 2 by 2 factorial design (Table 2) and geographic distribution of these areas is given (Fig. 1). Two blocks, proportionately equal in terms of number of ASHA workers (roughly equal to be number of villages) have been purposively paired and then randomly assigned to an interventional arm. Health infrastructure in each intervention arm is given in Fig. 2.

**Table 2 Tab2:** Design of the project

		PAS at APHCs/CHCs	
		Yes	No
PAS on VHND PLUSVillage IEC	No	Gosaiganj Block and Mall Block (Intervention1)	Bakshi Ka Talaab Block and Chinhat Block (Intervention 4)
	Yes	Malihabad Block and Mohanlalganj Block (Intervention3)	Sarojininagar Block and Kakori Block (Intervention2)

*Abbreviations PAS* Pneumonia Awareness Session, *VHND* Village Health and Nutrition Day, *IEC* information education communication, *PHC* Primary Health Centre, *APHC* Additional Primary Health Centre, *CHC* Community Health Center

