Univariate distribution of baseline and outcome variables would be assessed by frequency counts. Outliers will be identified, reported and excluded from analysis if required. They would be compared between interventions using chi square test for categorical and Student’s t test and ANOVA for continuous variables. A *p* value of < 0.05 will be taken as statistically significant, using a two tailed distribution. Adherence to the intervention across each arm will be calculated and compared across the three arms (as one was a control arm). Good intervention is defined as > 75% adherence to the sessions in the duration of the project. Primary outcomes will be number of PDK kits distributed to children plus the number of children treated by government functionaries for acute respiratory infection (ARI) or pneumonia without PDK, using medicines available at the health facility in interventions given by ANMs/ASHA workers. If we find that the diagnosis of children being treated is not mentioned, then we fill this missing information by extrapolation from data where diagnosis is given for the same month and within the intervention arm, assuming that there would be similar proportion of cases with this diagnosis. We will compute the difference in the proportion of ARI/pneumonia treated in each intervention arm when compared to control arm in the intention to treat analysis. For the secondary outcome, we will compare the proportion of cases with ARI/pneumonia treated by government providers as their first choice in interventions given by ANMs/ASHA workers, as an intention to treat analysis. In the per-protocol analysis we will compare the proportion of cases with ARI/pneumonia treated by government providers as their first choice in interventions given by ANMs/ASHAs from those households which have participated in the baseline as well end line survey using paired t-test. As a sub-analysis, we will compare the mean, median and interquartile range of out of pocket expenditure for ARI/pneumonia in the baseline and end line survey within each arm. As a comparator, we will do similar analysis for cases who have suffered from diarrhea to assess whether changes in spending were a function of time or because of care seeking from government providers, which is most inexpensive.

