A qualitative narrative of the process of establishment of the project will be given. Key informant and semi-structured interviews will be used to assess the level of satisfaction of stakeholders with (a) the services provided by public health facility augmentations and (b) IEC campaign strategies. Qualitative analysis techniques will be used for this data analysis.

Primary outcomes will be (a) number of patients of CAP treated by ANMs/doctors with medicines from PDK OR treated PMC OR PMU and (b) health service providers’ preference for treatment of CAP/ARI. For health facility utilization, the data will be abstracted periodically from the records maintained there. Feedback will be given to each facility on the process indicators within a month. For health provider preference, data from base line and end-line multistage cluster surveys will be used. At the end of the project the primary outcome measures will be compared in interventions given by ANMs/ASHA workers, using tests of proportion.

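### The facility-based primary outcome is a count, but it is to be compared as a proportion whose denominator is never stated

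*Protocol article*

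**What the plan says.** The facility outcome is worded as a count in three places in the protocol article.

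- Study aim: "Outcome measure will be number of CAP treated by ANMs/doctors with medicines from PDK or treated at either PMC or PMU".
- Data management & analysis plan, where the statistical methods are described: "Primary outcomes will be number of PDK kits distributed to children plus the number of children treated by government functionaries". The sentence goes on to cover children treated for ARI or pneumonia without a kit.
- The same section, where the primary outcomes are restated, as measure (a): "number of patients of CAP treated by ANMs/doctors with medicines from PDK OR treated PMC OR PMU". Measure (b) is provider preference, taken from the baseline and endline household surveys.

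The source for measure (a) is facility records: "For health facility utilization, the data will be abstracted periodically from the records maintained there". The section on the quarterly health facility audit lists what is abstracted: clinical pneumonia treated or referred, kit use, and availability of medicines and equipment.

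The planned comparison is nevertheless a proportion: "We will compute the difference in the proportion of ARI/pneumonia treated in each intervention arm when compared to control arm". The next sentence turns to the secondary outcome, so this one concerns the primary. At the end of the section both primary measures are to be compared "using tests of proportion".

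On infrastructure, the Table 1 footnote says "BKT Block has two CHCs. Other 7 blocks have one CHC each", and Table 2 places that block (Bakshi Ka Talaab) with Chinhat in the usual-care arm.

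**The concern.** A proportion needs a denominator, and none is named for the facility count. It could be the under-5 population, all community ARI/CAP cases in the arm, or all children treated at the facilities. These measure different things and can lead to different conclusions, and an analyst who has seen the data could choose among them.

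The outcome is meant to identify the communication strategy to be expanded to the whole district (Ethics and research governance) and offered for state scale-up (Post intervention phase). An ill-defined primary contrast could hide a true gain in care-seeking, or show a difference that reflects only the denominator or the size of the arm.

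**Working it through.** **1. Outcome against test.** Measure (b) has a natural denominator, the surveyed ARI/pneumonia cases, so a proportion fits it. Measure (a) is a count with no stated denominator, so a proportion and its test are undefined for it.

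**2. The one denominator hinted at.** The rule for missing diagnoses fills them from the share of cases with that diagnosis in the same month and arm. This suggests all treated children as a possible denominator, though the text never says so. Assumed figures, not in the documents: 200 ARI cases among 1,000 attendances.

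- All attendance rises by 30%: 260/1,300 = 20.0%, against 200/1,000 = 20.0% before. No effect is shown.
- Only ARI attendance rises by 30%: 260/(1,000 + 60) = 24.5%. The ratio is 24.5/20.0 = 1.23, a 23% relative gain instead of 30%.

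**3. The choice of denominator can change the sign.** Purely illustrative counts: 1,100 cases in an intervention arm and 1,200 in control.

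- All treated children (10,000 and 12,000): 11.0% − 10.0% = +1.0 point.
- Community ARI cases (9,000 and 8,000): 12.2% − 15.0% = −2.8 points.
- Under-5 population (40,000 each): 2.75% − 3.00% = −0.25 point.

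**4. CHCs by arm.** From the Table 1 footnote and Table 2, control has 2 + 1 = 3 and each other arm 1 + 1 = 2. The total is 2 + 2 + 2 + 3 = 9, which reproduces the figure in Table 1. At two earmarked beds per CHC (Table 3), control has 6 against 4. At 25 kits per CHC per month (Medicines), it has 75 against 50.

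**5. What that could do to raw counts.** Let s be the share of an intervention arm's cases treated at its CHCs. Assume equal volume per CHC and all else equal between arms. With no intervention effect, the ratio of control to intervention counts is 1 + 0.5s:

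- s = 0.10: 1.05
- s = 0.25: 1.125
- s = 0.50: 1.25
- s = 1.00: 1.50

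Scheduled kit supply gives another view. Assume the 28 APHCs and 331 ANMs are split equally, so 7 APHCs and 82.75 ANMs per arm. With 10 kits per APHC and 4 per ANM each month:

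- Control: 75 + 70 + 331 = 476
- Each other arm: 50 + 70 + 331 = 451
- Ratio: 476/451 = 1.055, or 5.5% more in control.

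Supply is not the same as cases treated, so neither calculation estimates the actual bias.

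**The case against.** This is a condensed article, and the exact denominator may sit in a fuller protocol or analysis plan. That would excuse silence. It does not excuse a stated outcome and a stated test that do not fit each other.

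Several stronger conclusions are tempting, and the documents do not support them.

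- A reader might infer that no denominator could be had. The diagnosis rule implies records of treated children beyond ARI, and the household surveys measure ARI/CAP burden before the intervention, with a similar survey afterwards. The defect is that the denominator is not named.
- A reader might infer that control counts are inflated by half. The 1.5 ratio applies to CHCs alone. APHCs and ANMs also contribute, kits are replenished on demand, and the two CHCs in one block may share that block's cases.
- A reader might infer that the arms are known to differ in size. No arm-level child population is given in the text, and Fig. 2, which shows infrastructure by arm, is not available here.
- A reader might infer that children are credited to the wrong arm when they cross block boundaries. Nothing in the text shows that this is material, or that the case sheet omits residence.

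It is also fair to say that a uniform 30% rise in attendance is an extreme case, since the session content is specific to pneumonia, and that the effect remains visible if only ARI attendance rises. The illustrations show what could happen, not what is expected.

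**Conclusion.** The point stands in a limited form. The facility outcome is a count, the planned contrast and test are for proportions, and no denominator is stated, so the primary comparison cannot be calculated as written. This conclusion rests on the text alone.

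The denominator that the text hints at would measure case mix rather than care-seeking. Falling back on raw counts is unsafe. Pairing blocks on ASHA numbers does not make arms equal in under-5 children, and the 3-against-2 CHC split would act against the interventions if the extra CHC draws additional cases. The size of that bias is unknown. Under the assumptions shown it runs from 5% to 50% as the CHC share of cases goes from 10% to 100%, and it could be smaller still if the two CHCs divide one block's cases.

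**What to change.** For the facility outcome, replace both references to proportions with a rate: cases treated by public providers per 1,000 under-5 children per month, by block, with a named source for block under-5 population. Settle one case definition, because the statistical methods text counts ARI or pneumonia while the Study aim and the restated outcome count CAP.

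Compare block-level rates, preferably on the log scale, with the block as the unit of analysis. If a Poisson or negative binomial model with a log child-months offset is preferred, it must allow for between-block variation. Otherwise it will overstate precision.

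Keep a test of proportions for the survey measure only, in a form that respects the sampling clusters and the allocated blocks. Recording block of residence on the case sheet is optional.

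The cost is small: a revised outcome definition and analysis paragraph, and block population figures. The downsides are that under-5 populations are projections with some error, and that intervals will be wide. With 8 blocks in 4 arms, only 8 − 4 = 4 degrees of freedom remain for between-block error. That limit comes from the design; the rate only makes it visible.

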#### Post intervention phase (6 months)

Post-intervention, primary outcome measures, e.g. utilization of public facility for management of CAP will be assessed through health facility audit. End line survey, similar to baseline survey, will be conducted to measure the changes due to proposed intervention in community’s preference of health providers for treatment of ARI/CAP. Data management, analysis and report writing will be done. Results will be widely disseminated. For widespread dissemination, study protocol and findings will be published in indexed peer-reviewed journals. Technology transfer will be done to the state government to scale up establishment of PMC, PMU and provide PDK plus implementing the most effective behavior change communication strategy for the entire state. Data will be accessible to public researchers after the study findings have been published.

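### No stated analysis compares change between arms, although the second objective is pre/post change and both surveys are run in every arm

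*Protocol article*

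**What the plan says.** In the Protocol article, Study aim makes change in the type of provider used, before versus after the intervention, the second objective. Post intervention phase gives the second survey the same purpose: "End line survey, similar to baseline survey, will be conducted to measure the changes due to proposed intervention". Pre-intervention phase has the baseline survey done in intervention and control areas.

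Data management & analysis plan then states these analyses of the survey data:

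- **Intention to treat, provider preference:** "we will compare the proportion of cases with ARI/pneumonia treated by government providers as their first choice in interventions given by ANMs/ASHA workers".
- **Per protocol, provider preference:** the same proportion, "from those households which have participated in the baseline as well end line survey using paired t-test".
- **Out-of-pocket spending, a sub-analysis:** mean, median and interquartile range, "in the baseline and end line survey within each arm". A similar analysis of diarrhoea cases is added "to assess whether changes in spending were a function of time or because of care seeking from government providers".
- **Outcome paragraph just before Process indicators:** "For health provider preference, data from base line and end-line multistage cluster surveys will be used", and outcomes are compared between interventions by tests of proportion.

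Study design assigns two blocks to each arm, paired on the number of ASHA workers. Under Intervention phase, the usual care arm also receives the drug kits, management corners and management units. Ethics and research governance looks to that arm to show whether better facilities alone raise care seeking.

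**The concern.** The objective and the stated analyses do not meet. A question about change, asked in a trial with a concurrent control arm and two survey rounds, calls for the difference between arms in change. The plan has a between-arm comparison that names no baseline term, and before-after comparisons that name no control arm.

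Two different problems follow. In the between-arm test, blocks that already differed in use of government providers carry that difference into the result. In the before-after analyses, each arm's change contains everything that changed over the period, including a facility package given to all arms. The plan itself expects that package may shift care seeking.

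Provider preference is called secondary in one paragraph of the analysis section and primary in another, so the gap may affect a primary outcome. The best communication strategy is also meant to be scaled up to the whole state.

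**Working it through.** The article gives no power calculation, block variance or intracluster correlation (ICC), so there is no figure of its own to reproduce.

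**1. What each stated comparison estimates**

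Write the change from baseline to end line in an arm as package effect + general trend + that arm's communication effect. Usual care has the first two only.

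| Stated analysis | Contrast | What it contains |
|---|---|---|
| Intention to treat, tests of proportion | Between arms, no baseline term | Communication effect + chance block difference; package and common trend cancel |
| Per protocol, paired t-test | Before-after, repeat households | Communication effect + package + trend |
| Spending | Before-after within arm | Communication effect + package + trend |
| Diarrhoea comparator | Before-after within arm | Trend in diarrhoea spending + any shift in diarrhoea care |
| Not stated: difference in change against usual care | Between arms and rounds | Communication effect; package, common trend and stable block differences cancel |

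Subtracting the diarrhoea change informally removes trend only if both conditions share it. It does not separate communication from package. If diarrhoea care also moves to cheaper government providers, part of a real effect would be read as time.

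**2. Size of the block difference in the between-arm test**

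From the documents: 8 blocks, 4 arms, 2 blocks per arm; 2400 households in 240 villages. If these are spread equally, there are 2400/8 = 300 households per block. Everything else is assumed.

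With between-block standard deviation s and independent blocks, the chance difference between two arms has standard deviation s × √(1/2 + 1/2) = s. An assumed s of 5 to 10 points gives 5 to 10 points. Alternatively take s = √(ICC × p(1−p)):

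- p = 0.2, ICC 0.005: √(0.005 × 0.16) = 2.8 points
- p = 0.2 to 0.4, ICC 0.01: 4.0 to 4.9 points
- p = 0.4, ICC 0.05: √(0.05 × 0.24) = 11.0 points

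**3. What using baseline does to that variance**

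Let r be the baseline to end-line correlation of block values. The between-block variance is multiplied by 2(1−r) for a change contrast and by 1−r² for baseline adjustment with a known slope.

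| r | Change contrast, 2(1−r) | Baseline adjustment, 1−r² |
|---|---|---|
| 0.5 | 1.00 | 0.75 |
| 0.7 | 0.60 | 0.51 |
| 0.9 | 0.20 | 0.19 |

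The change contrast also doubles the within-block sampling variance. Standard errors in points for p = 0.2 and m = 150 illness cases per block per round (both assumed):

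| ICC | End line only | Change, r = 0.5 | r = 0.8 | r = 0.95 |
|---|---|---|---|---|
| 0.005 | 4.3 | 5.4 | 4.9 | 4.7 |
| 0.01 | 5.2 | 6.1 | 5.2 | 4.8 |
| 0.02 | 6.5 | 7.3 | 5.8 | 4.9 |
| 0.05 | 9.5 | 10.0 | 7.2 | 5.3 |

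Total variance breaks even at r = 0.5 + (1−ICC)/(2 × m × ICC). With m = 150 this is 0.5 + 0.99/3 = 0.83 at ICC 0.01, and 0.5 + 0.95/15 = 0.56 at ICC 0.05. At ICC 0.005 it exceeds 1, so the change contrast never gains overall precision there.

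**4. Degrees of freedom**

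With 8 blocks and 4 arms, a baseline covariate takes residual degrees of freedom from 4 to 3 and the critical t from 2.78 to 3.18, a factor of 1.15. At r = 0.5 the between-block standard deviation falls by √0.75 = 0.87, so interval width changes by about 1.15 × 0.87 ≈ 0.99, before error in estimating the slope. If the pair is the randomised unit, four units with two main effects leave 1 degree of freedom, and a covariate leaves none.

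**The case against.** A reader might infer several stronger criticisms. The documents do not support them.

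- **That baseline is ignored.** It is not. The article says both surveys will be used for provider preference, and the per-protocol analysis needs both. How baseline enters the between-arm comparison is what is missing. Such detail is often left to an analysis plan, but here the article does name a method, and a test of proportions takes no covariate.
- **That secular trend distorts the intention-to-treat comparison.** A trend common to all blocks cancels in a concurrent comparison with usual care. The trend objection reaches only the paired and spending analyses.
- **That the between-arm contrast is biased.** Under random allocation it is unbiased over allocations. Chance imbalance costs precision and calls for block-level standard errors. A test that ignores clustering would exceed its nominal 0.05, but that is a separate defect which baseline data do not cure.
- **That change in spending is tested only within arms.** It is a sub-analysis of summary statistics with no test named in that sentence. Control-arm figures will appear beside the others, and the plan recognises time trend by adding diarrhoea.

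The diarrhoea safeguard is real but partial. It too is within arm, with no formal contrast. That diarrhoea care might shift is plausible rather than documented; the rationale for behaviour change communication does expect the sessions to build confidence in public services generally, not for pneumonia alone.

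The objection that precision may not improve also stands, as the working shows.

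**Conclusion.** The point holds in a limited form. The objective is change, the data and the control arm to estimate it are planned, and no stated analysis compares change between arms.

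For the between-arm test the consequence is imprecision: chance block differences with a standard deviation of about 2.8 to 11.0 points remain in it, assuming p of 0.2 to 0.4, ICC of 0.005 to 0.05 and independent blocks within an arm. Matching on ASHA numbers alone gives no assurance that care-seeking is balanced.

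For the paired and spending analyses the consequence is interpretive: a within-arm change cannot be credited to the communication strategy. This conclusion needs no assumed figure. It follows from the package being given to all arms, and it is the firmer reason for the change. The precision gain depends on an unknown block-level correlation and may be nil or negative for a change contrast. All standard deviation, ICC, prevalence, case-count and correlation values are assumptions.

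**What to change.** For provider preference and for out-of-pocket spending, state that the estimate of interest is the difference between each communication arm and usual care in change from baseline to end line. Choose one form in advance:

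- an arm-by-survey-round contrast, with clustering by block and village respected; or
- the block's end-line value adjusted for its baseline value, analysed at block level.

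Recast the repeat-household analysis as a between-arm contrast of within-household change. Keep the diarrhoea comparison as a supporting check, set out against usual care in the same way. Reconcile the two paragraphs of the analysis section so that they agree on how the baseline survey is used.

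The cost is analysis wording, since both surveys are already planned. There is a statistical price: a change contrast adds baseline sampling error and reduces between-block variance only if the block-level correlation exceeds 0.5, while block-level adjustment spends one of very few degrees of freedom. Neither cures having two blocks per arm, so the intervals should be reported with that limit stated.

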### Adverse events monitoring

Approximately 5% of caregivers of cases of CAP who have received PKD will be contacted. They will be asked about their perceptions of the medicines and cards provided in the kit, whether the child required hospitalization or improved after taking medicines and if the child had diarrhea, rash, vomiting or any other complaints. This will be done by visiting their homes.

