### Ethics and research governance

This study (protocol version 2 dated 19.12.2015) has been approved by the Health Ministry Steering Committee of the Indian Council of Medical Research, New Delhi (India), the Institutional Ethics Committee, King George’s Medical University (KGMU), Lucknow (India) and relevant public authorities of state government. Written informed consent will be obtained by the project staff from all participants. To protect confidentiality of respondents, their identifiers will not be noted in any data collection instrument. Visit Log books, questionnaires, and project documents will be stored in a locked area, not accessible to unauthorized individuals.

Technical Advisory Group (TAG) for the project will be constituted to ensure quality control and government buy-in for the research findings. Members from government and non-government sectors, civil society organizations, grass root workers, academia and sponsors will be part of TAG. This group will meet twice, first at the time of project initiation and then immediately before project completion.

To ensure that the entire community of the district of Lucknow is benefitted through improved delivery of pneumonia specific health care by the public health system, PMU, PMC and PMKs will be provided to all the CHCs, APHCs, and SC of Lucknow District. This will ensure equity and distributive justice. However, there is doubt about the best way of community mobilization. The availability of better care facilities alone may drive improved care seeking for CAP. If that is the case, we have a usual care arm in our behavioral trial. If this is not the case, we will try out three other interventions, first public health facility based (CHC/APHC), second village based and the third a combination of both. The most effective strategy for improved care seeking of CAP (as a result of behavior change) will be identified and expanded into the entire district.

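### The analysis called per-protocol is a both-surveys household panel tested before-after within households, so it neither reflects adherence nor compares arms, and no household link is described

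*Protocol article*

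**What the plan says.** All on the government-provider-as-first-choice outcome, from the Protocol article:

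- **Data management & analysis plan.** An intention-to-treat comparison comes first. Then: "In the per-protocol analysis we will compare the proportion of cases with ARI/pneumonia treated by government providers as their first choice", restricted to records "from those households which have participated in the baseline as well end line survey using paired t-test". The sentence sets this up as a comparison across the interventions delivered by ANMs and ASHAs.
- **Same section, on adherence.** "Adherence to the intervention across each arm will be calculated and compared across the three arms", followed by "Good intervention is defined as > 75% adherence to the sessions in the duration of the project". Neither sentence is tied to the per-protocol set.
- **Pre-intervention phase.** 2400 households from 240 villages are surveyed at baseline.
- **Post intervention phase.** The endline survey is described only as resembling the baseline one. A return to the same households is not stated.
- **Ethics and research governance.** "To protect confidentiality of respondents, their identifiers will not be noted in any data collection instrument". The next statement is that "Visit Log books, questionnaires, and project documents will be stored in a locked area". No household code or linkage step is described.
- **Intervention phase and Ethics and research governance.** Drug kits, management corners and management units go to every arm. The usual-care arm gets these and no awareness sessions.

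**The concern.** There are three problems.

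1. **The label.** A per-protocol set is one selected by what was received. This one is selected by presence at two surveys. A household that never attended an awareness session qualifies if it was interviewed twice. A regular attender missed at one survey does not.
2. **The test.** The trial asks which communication strategy works better than usual care. A paired t-test on the same households asks whether anything changed between the two surveys.
3. **The link.** Pairing requires returning to the same households and joining two records. The article states neither step, and its confidentiality rule appears to exclude the most obvious joining key.

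A before-after trend in a selected subset could therefore be reported under a heading that readers take to mean the effect under good adherence. The most effective strategy is to be expanded, so that matters. The outcome is also not minor: one paragraph of the analysis section calls it secondary, and a later one lists it as primary outcome (b). A key that is not created at baseline may not be recoverable later.

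**Working it through.** **Survey size.** 240 villages / 8 blocks = 30 per block, which matches the 30-cluster method if it is applied in each block (an inference). 2400 / 240 = 10 households per village. 2400 / 4 arms = 600 households per arm.

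**What the paired test estimates.** Let s be the change over time that would have happened anyway, i the effect of the infrastructure package given everywhere, and b the effect of one arm's communication strategy.

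- Before-after change in a session arm: s + i + b
- Before-after change in usual care: s + i
- Difference in change: (s + i + b) − (s + i) = b

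The paired test targets the first or second line. The trial question is the third.

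The surveys span the infrastructure change. Provider use is asked over the last 12 months (Study aim). Assume the phases of 6, 12 and 6 months run consecutively and the strengthening is complete by month 6.

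- Baseline falls at or before month 6, so at least 12 − 6 = 6 months of its recall window precede the project.
- Endline falls at month 18 or later, so its window opens no earlier than 18 − 12 = month 6, wholly after the strengthening.

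So i sits inside every arm's before-after change.

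**Invented illustration.** In one arm, take 600 pairs, of which 60 move to a government provider and 40 move away. Change = (60 − 40)/600 = 3.3 percentage points, paired t-test p = 0.0454. If the same happened in all four arms, each would pass the plan's 0.05 level, yet every arm's change minus usual care's would be 3.3 − 3.3 = 0.

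**Is a t-test on yes/no data the problem?** Three invented examples (n; moves to; moves away):

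| n | to | away | paired t p | McNemar p |
|---|---|---|---|---|
| 600 | 60 | 40 | 0.0454 | 0.0455 |
| 300 | 40 | 25 | 0.0627 | 0.0628 |
| 100 | 20 | 10 | 0.0676 | 0.0679 |

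They agree to within 0.001. The fault is the missing arm contrast.

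**What pairing needs.** Rural population = 4,589,838 × 0.3379 = about 1,550,906 (Study setting & participants). Assume household size 5 to 7, 30% to 100% of households eligible, and about one village per ASHA (1246, Table 1). Eligible households N then run from 1,550,906 / 7 × 0.3 = 66,467 to 1,550,906 / 5 = 310,181.

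- Fresh endline draw: expected overlap 2400² / N = about 19 to 87 households, or 5 to 22 per arm.
- Same villages, fresh households: 240 × 10 × 10 / (N / 1246) = about 96 to 450, or 24 to 112 per arm.

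A usable panel therefore needs a planned return to the baseline households.

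**Usable pairs if they are revisited.** A pair exists only if the household has a case in both rounds. Assume 80% are found again and a share p has a case in each round, independently: 600 × 0.8 × p².

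| p | pairs per arm | share of 600 |
|---|---|---|
| 0.3 | 43 | 7% |
| 0.5 | 120 | 20% |
| 0.7 | 235 | 39% |

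Only the 600 comes from the protocol. The 12-month recall could make p higher, and recurrent illness within households would raise the counts, so these are illustrations and not forecasts.

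**The case against.** The strongest reply is that the analysis is feasible and only supportive. The confidentiality rule concerns respondents' identifiers on instruments. It does not forbid a coded household number or a key held elsewhere, and locked visit logs and written consents exist outside the questionnaires. Naming households that took part in both surveys implies some linkage, and an article may leave its mechanics to the full protocol. This stands. A reader might infer from the identifier rule that the analysis cannot be done, and the documents do not support that. They support only that linkage is required, that none is described, and that the passages need reconciling.

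Three other inferences also go too far:

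- **That the 75% threshold is never used.** It follows directly on the comparison of adherence across the three session arms and serves as the benchmark for it. Adherence is to be reported by arm, so no household-level criterion was at hand and ignored.
- **That the adverse-event home visits face the same obstacle.** The plan is that "Approximately 5% of caregivers of cases of CAP who have received PKD will be contacted". These caregivers received drug kits and can be reached through treatment records without the survey questionnaires.
- **That per-protocol should mean more than 75% adherence by block.** With two blocks per arm this could remove half or all of an arm, and it has no meaning in usual care, which has no sessions.

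It is also fair that an intention-to-treat analysis of this outcome stands beside this one, that the set is openly defined by survey participation, and that an equal rise in all four arms would be visible to a careful reader. None of this answers the first two problems. The article itself fixes the label, the set and the test, and following them yields no between-arm estimate. The plan does guard against time trends in spending, with a diarrhea comparator, but names no such guard here.

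**Conclusion.** The point holds for the label and the test, and in a limited form for the link.

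- **Label:** wrong on the face of the text. The set is a panel subset, not one defined by receipt of the intervention or adherence to it.
- **Test:** it answers a different question. It measures time trend plus infrastructure effect plus any communication effect, and the first two are present in all arms. The size of that bias cannot be derived from the documents.
- **Link:** unreconciled rather than impossible. The sections on analysis, the endline survey and confidentiality do not yet fit together.

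The number of pairs is unknown. The overlap and pair counts show only that a deliberate return visit is needed and that the two-case requirement can thin the set. They rest on assumed household size, eligibility, re-contact and illness frequency. The effect is confined to a supportive analysis of provider choice and leaves the facility-based count outcome untouched. It should be corrected, since the change is cheap.

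**What to change.** 1. Rename it a panel-household analysis, supportive of the intention-to-treat analysis.
2. Replace the paired t-test with the between-arm difference in change in the binary first-choice outcome: arm, survey and arm-by-survey terms, allowing for repeated households and clustering, with inference that recognises only two blocks per arm.
3. State that endline returns to the baseline households, linked by an anonymous household code on both questionnaires, with the code-to-household key held separately under lock. Say in the ethics section that such a code is used, so that it agrees with the analysis and endline-survey sections.
4. Call no result per-protocol unless its set is defined by exposure to sessions. Such a definition can apply only to the three session arms.
5. Report how many panel households had an ARI or pneumonia case in both rounds.

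Cost: one code field, a locked key file, and a few sentences of analysis and ethics text. The downsides are a small confidentiality burden, fewer usable pairs than households surveyed, and limited precision for arm contrasts with two blocks per arm.
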